### Sample size

The primary outcome is the binary measure of pancreatic leak or no leak. Current experience suggests the present rate of leak is 20 % in the standard treatment; a reduction to a 10 % rate in the trial treatment is of clinical importance. A sample size of 208 patients per group would allow a two-sided, two-sample test for binomial proportions to detect a difference in proportions of 10 % (10 % versus 20 %) with power of 80 % and significance level of 0.05. The sample size calculation was based on an O’Brien-Fleming two-stage design with binding futility boundaries (SAS PROC SEQDESIGN version 9.3). Non-compliance would occur in the event of unresectable disease at laparotomy (estimated at 15 %) with a further assumed loss to follow-up of 3 %, giving an overall sample size of 253 per group (506 in total).

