### Randomization

Randomization will be undertaken intra-operatively by the surgeon following pancreatic head excision and just prior to pancreatic remnant reconstruction. Hence, the surgeon will only randomize the participant if they feel at complete equipoise and are happy to perform either anastomosis. Randomization will take place via a password-protected web-based tool called the Treatment Allocation Randomization System (TARDIS) developed, maintained and controlled by Liverpool Cancer Trials Unit’s IT Department. Patients will be randomized to one of the treatment groups in a 1:1 ratio, with the following stratification factors: (1) research site, (2) pancreatic texture: soft versus normal/hard, and (3) pancreatic duct diameter: 3 mm or >3 mm.

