### Statistical methodology

Formal interim statistical monitoring of the accumulating data will be performed at regular intervals and reviewed by an Independent Data Monitoring and Safety Committee (ISDMC). In addition, the design allows for an interim analysis with possible early stopping after results for 208 patients are available. At this stage, based on an O’Brien-Fleming two-stage design, if the standardized *Z* value lies in the interval (−0.698, 0.698) then the trial is stopped for acceptance of the null hypothesis of equal proportions. If the standardized *Z* value is less than −2.736 or greater than 2.736 then the trial is stopped accepting one proportion is significantly less than the other. Otherwise the trial continues to the final stage where the test for the standardized *Z* value will have acceptance region for the null hypothesis of (−1.934, 1.934). Values outside this region will indicate significantly different proportions. (SAS PROC SEQDESIGN version 9.3 was used for the design.)

Early stopping rule: the first 6 months of the study will be run as a feasibility/pilot study with a decision, whether to continue or not, made at that point. Two sites will be opened initially for this feasibility/pilot phase. The decision whether to continue or not will be based on the number found to be eligible across the two sites, the number enrolled, the number randomized and the number who took up the randomization. If the number enrolled at 6 months is less than 40 patients, then a decision will be made as to whether to continue the trial or not. If the recruitment rate is acceptable then the other sites will be opened, with an expected number of patients at 12 months of 137 across all sites.

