**Fig. 3 Fig3:**
[figure not shown]
PANasta logo

This study is ambitiously intending to randomize over 500 patients undergoing pancreatic surgery. These numbers are powered to detect a 10 % absolute point reduction in the primary endpoint of POPF – which is a relevant difference in surgical trials. Included is a generous dropout rate and account is also taken of patients who are not randomized if unresectable disease is encountered at laparotomy. Furthermore, randomization will be undertaken following resection, just prior to pancreatic anastomosis; therefore, maximising surgeon equipoise. One of the prime reasons that the current medical literature base on pancreatic anastomosis is so poor is the lack of operative standardization not only between individuals but also between centers. In order to diminish this as much as is possible a number of safeguards are built into this study: notably incorporation of a feasibility pilot study within the first 6 months; a pre-pilot consensus meeting; formulation of an operative manual and operative photographs.

The internal pilot will run in two centers initially and will evaluate in step-wise fashion: (1) the number of patients eligible at each site; (2) the number of patients consented; (3) the number of patients randomized; and finally (4) the number of patients who took up the randomization. This will inform us of the real figures for stopping this trial for futility in recruitment. In addition, an interim analysis will be undertaken once 208 patients have been randomized.

The pre-pilot consensus meeting was attended by the research site principal investigators (PIs), who agreed that the use of octreotide, pancreatic duct stents and post-operative drains were to be used in *all* patients. The steps of each anastomosis were discussed and agreed. The adherence to these steps will be reviewed at the end of the internal pilot phase and the manual and protocol modified as necessary.

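### The 253 per group (506) includes a 15 % allowance for patients who are never randomised, so it fits the design as an enrolment figure and not as the randomised target it is presented as

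*Protocol article*

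**What the plan says.** The Sample size section of the protocol article starts from 208 patients per group: "A sample size of 208 patients per group would allow a two-sided, two-sample test for binomial proportions", for leak rates of 20 % and 10 %, 80 % power and a two-sided 0.05 level, under a two-stage O'Brien-Fleming design with binding futility. It then makes two allowances. One is 15 % for unresectable disease, described as non-compliance: "Non-compliance would occur in the event of unresectable disease at laparotomy". The other is 3 % for loss to follow-up. The result is 253 per group, 506 in total, and the Abstract repeats the 253 per group.

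The Randomization section fixes the moment of allocation: "Randomization will be undertaken intra-operatively by the surgeon following pancreatic head excision and just prior to pancreatic remnant reconstruction".

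The Discussion makes two statements in one paragraph. The first is "This study is ambitiously intending to randomize over 500 patients undergoing pancreatic surgery". The second is that "account is also taken of patients who are not randomized if unresectable disease is encountered at laparotomy".

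The Statistical methodology section places the interim analysis after results for 208 patients. Further on, it describes a formal analysis of the primary endpoint once half the patients have been recruited. It also sets the pilot threshold ("If the number enrolled at 6 months is less than 40 patients") and expects 137 patients at 12 months.

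**The concern.** A patient found unresectable at laparotomy does not have the pancreatic head removed, so that patient never reaches the point of randomisation. Such a patient cannot be a non-complier within a group, and a per-group number should not be inflated for the loss. The 15 % belongs between enrolment and randomisation; only the 3 % falls after it.

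The Discussion shows the conflict directly. If the allowance covers patients who are not randomised, the number that contains the allowance is not the number randomised.

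At stake is the recruitment end point. Sites and oversight committees cannot tell from the article whether accrual is complete at 430 or at 506 randomised patients. The interim is affected too: 208 patients are half of the evaluable total under one reading but not under the other.

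**Working it through.** **Inputs.** From Sample size: leak rates 0.20 and 0.10, 208 evaluable per group, 15 % unresectable, 3 % lost to follow-up, stated target 253 per group (506). From Statistical methodology: interim at 208 patients, stop for futility if |Z| < 0.698, stop for a difference if |Z| > 2.736, final critical value 1.934.

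**1. Does 208 per group reproduce?** I used a bivariate normal calculation with the printed boundaries, unpooled variance and information fraction 0.5.

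- Variance term: 0.20 × 0.80 + 0.10 × 0.90 = 0.25.
- Expected final Z: 0.10 / √(0.25/208) = 2.884. Expected interim Z: 2.884 × √0.5 = 2.040.
- Result: two-sided type I error 0.0501, power 80.1 %.

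So 208 per group reproduces, with the interim at 208 of 416 (50 %).

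**2. Does 253 per group reproduce?** 208 / (0.85 × 0.97) = 252.3, rounded up to 253; 2 × 253 = 506. It reproduces exactly, which shows that the 15 % was applied to the per-group number.

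**3. How many must be randomised?** After randomisation only the 3 % applies: 208 / 0.97 = 214.4, so 215 per group and 430 in total. The difference is 506 − 430 = 76, or 76/430 = 18 %.

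**4. Read 506 as enrolled.** 506 × 0.85 = 430 randomised; 506 × 0.85 × 0.97 = 417 evaluable, against 416 needed. Power, boundaries and the interim at 208 all agree.

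**5. Read 506 as randomised.** 506 × 0.97 = 491 evaluable, about 245 per group. Enrolment would have to be 506 / 0.85 = about 595, a figure that the article does not give. The operating characteristics then depend on interim timing:

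| 506 is read as | Evaluable | Interim | Information fraction | Two-sided type I error | Power |
|---|---|---|---|---|---|
| Enrolled | about 416 | 208 patients | 0.50 | 0.050 | 80 % |
| Randomised | about 491 | 208 patients | 208/491 = 0.42 | 0.048 | 84 % |
| Randomised | about 491 | half of 491 | 0.50 | 0.050 | 86 % |

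**The case against.** The strongest reply is that 506 is simply the enrolment target, and that only its label is at fault. Much of this stands. The arithmetic is correct, and Table 2, the pilot rules and the Trial status section all treat enrolment and randomisation as separate steps. The Discussion says that the allowance is for patients who are not randomised, and the interim at 208 is exactly half of 416. What does not stand is the label: groups exist only after randomisation, so 253 *per group* cannot be an enrolment figure, and the Discussion says outright that over 500 will be randomised. On this reading too, the Abstract, Sample size section and Discussion need correcting.

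A reader might infer more than the document supports:

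- **That the trial has the wrong power or an inflated error rate.** It does not. On either reading power is at least 80 % and the two-sided error stays at about 0.05 or just below.
- **That the randomised target is definitely too large by 76.** That holds only if 506 are really to be randomised, which the article leaves unsettled.
- **That the interim falls at 42 % of the information.** This needs 506 randomised and the interim held at 208. The article also mentions an analysis at half of recruitment, which would keep the fraction at 50 %.
- **That the trial is lengthened by a calculable number of months.** An accrual rate derived from 137 and 506 assumes that both count the same population and that accrual is steady; neither is stated.
- **That CONSORT denominators are affected.** Those are observed counts and do not depend on the planned target.
- **That the pilot threshold of 40 is ambiguous.** The text says that it counts patients enrolled. Only the 137 is left open.

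**Conclusion.** The concern holds as a contradiction about which population 506 describes. The number contains a 15 % loss that occurs before randomisation, so it cannot be the randomised per-group target that the Abstract, Sample size section and Discussion present. Using the protocol's own 15 % and 3 %, the consistent chain is about 506 enrolled, 430 randomised (215 per group) and about 416 evaluable (208 per group).

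If 506 were randomised, the excess would be 76 patients, with power of about 84 % (interim at 208) or 86 % (interim at half of the evaluable total). These powers rest on leak rates of 20 % and 10 %, unpooled variance and the printed boundaries. The error is conservative and leaves statistical validity intact; the harm is an unclear recruitment end point. Severity: should-fix.

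**What to change.** If 506 is the enrolment number, which is the reading that the design figures support:

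- State the chain in the Sample size section: about 506 enrolled, 430 (215 per group) randomised, 416 (208 per group) evaluable.
- Remove *per group* from 253 there and in the Abstract, and describe unresectable disease as loss before randomisation instead of non-compliance.
- Correct the Discussion sentence about randomising over 500.
- Say whether the 12-month figure of 137 counts enrolled or randomised patients.

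If the sponsor does intend to randomise 506, it should instead state about 595 enrolled, restate the power, and align the interim with half of the resulting evaluable total, about 245 of 491.

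The first route costs a wording amendment and no extra patients. The second also needs about 89 more enrolments than 506 (595 − 506) and a revised statement of the interim.

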### Randomization

Randomization will be undertaken intra-operatively by the surgeon following pancreatic head excision and just prior to pancreatic remnant reconstruction. Hence, the surgeon will only randomize the participant if they feel at complete equipoise and are happy to perform either anastomosis. Randomization will take place via a password-protected web-based tool called the Treatment Allocation Randomization System (TARDIS) developed, maintained and controlled by Liverpool Cancer Trials Unit’s IT Department. Patients will be randomized to one of the treatment groups in a 1:1 ratio, with the following stratification factors: (1) research site, (2) pancreatic texture: soft versus normal/hard, and (3) pancreatic duct diameter: 3 mm or >3 mm.

### Blinding

Patients and all team members except for the surgeons will be blinded to the intervention. In order to maintain the blinding for the patient and other site staff, the surgeon will not write which anastomosis has been performed in the surgical notes but rather this will be recorded in the notes as “anastomosis constructed as per PANasta trial randomization.” Serious adverse events (SAEs) will be assessed blinded, and only if deemed necessary would un-blinding occur, i.e., if subjects require life-saving surgery in a district hospital. This, however, would be a rare event. Adverse event (AE) and SAE reporting would follow as soon as is practical. This will not have any impact on the endpoint assessment of the patient.

### Data management

This study is run from the Liverpool Cancer Trials Unit (LCTU). The study CRF is the primary data collection instrument for the study. CRF pages will be available for sites to download from the LCTU portal: http://www.lctu.org.uk.

Individual participant medical information obtained as a result of this study is considered confidential and disclosure to third parties is prohibited. CRFs will be labelled with patient initials and unique trial screening and/or trial number. Intra-operative photographs will be transferred to the LCTU and will be identifiable by unique trial number only. Histological slides will be transferred to the Department of Pathology at the Royal Liverpool University Hospital and will be identifiable by unique trial number only. Blood samples will be transferred to the University of Liverpool GCLP laboratory and will be identifiable by unique trial number only. Consent forms sent to the LCTU as part of the randomization process may contain patient identifiers for the purpose of monitoring as described in the trial risk assessment. Such information will be stored in secure, locked cabinets.

### Withdrawals

If voluntary withdrawal occurs, the patient will be asked to allow continuation of scheduled evaluations, complete an end-of-study evaluation, and be given appropriate care under medical supervision until any AE symptoms resolve or the subject’s condition becomes stable. Subjects are free to leave the trial at any point without the need to give reasons for their decisions. If voluntary withdrawal occurs prior to the surgical intervention the patient will not be randomized and no further trial data will be collected on that patient. Patients may wish to withdraw from the trial following the surgical intervention. In such cases no further data should be collected but data up to this time can be included in the trial if anonymized. Patients may also wish to remove all data and/or any samples collected up to the point of withdrawal from the trial analysis. In these cases an End of Study Form along with the reason for withdrawal will be submitted to the LCTU. However, safety data that have been sent to regulatory authorities prior to that point (e.g., Annual Safety Reports to Research Ethics Committee) will not be withdrawn. For patients moving from the area, every effort should be made for the patient to be followed-up at another participating trial center and for this trial center to take over responsibility for the patient or for follow-up via the GP.

### Statistical methodology

Formal interim statistical monitoring of the accumulating data will be performed at regular intervals and reviewed by an Independent Data Monitoring and Safety Committee (ISDMC). In addition, the design allows for an interim analysis with possible early stopping after results for 208 patients are available. At this stage, based on an O’Brien-Fleming two-stage design, if the standardized *Z* value lies in the interval (−0.698, 0.698) then the trial is stopped for acceptance of the null hypothesis of equal proportions. If the standardized *Z* value is less than −2.736 or greater than 2.736 then the trial is stopped accepting one proportion is significantly less than the other. Otherwise the trial continues to the final stage where the test for the standardized *Z* value will have acceptance region for the null hypothesis of (−1.934, 1.934). Values outside this region will indicate significantly different proportions. (SAS PROC SEQDESIGN version 9.3 was used for the design.)

Early stopping rule: the first 6 months of the study will be run as a feasibility/pilot study with a decision, whether to continue or not, made at that point. Two sites will be opened initially for this feasibility/pilot phase. The decision whether to continue or not will be based on the number found to be eligible across the two sites, the number enrolled, the number randomized and the number who took up the randomization. If the number enrolled at 6 months is less than 40 patients, then a decision will be made as to whether to continue the trial or not. If the recruitment rate is acceptable then the other sites will be opened, with an expected number of patients at 12 months of 137 across all sites.

The trial will be analyzed and reported following the Consolidated Standards of Reporting Trials (CONSORT) guidelines [44, 45]. All statistical analyses will be on an intention-to-treat basis. Missing data, which are anticipated to mainly affect the quality of life outcome measure, will be handled by considering the robustness of the complete case analysis to sensitivity analyses using different imputation assumptions informed by data collected on reasons for missing data. Continuous variables will be summarized by descriptive statistics (mean, standard deviation, minimum, median and maximum) and frequency tables will be provided for categorical data. The two-sided, two-sample test for binomial proportions will be used to test for a difference in the probabilities of leak/fistula occurrence between the two arms. Sensitivity analysis will be performed using the continuity-corrected Cochran-Mantel-Haenszel (CMH) test calculated over the recruiting centers. Logistic regression will be used to investigate the variation in these probabilities by center. The secondary endpoints will be analyzed using summary statistics, CMH tests, logistic regression, analysis of variance and multi-variate methods as appropriate. As the two procedures are standard practice, a formal analysis of the primary endpoint only will be undertaken when half the patients have been recruited. Quality of life measurements will be assessed over time and comparisons made between treatment groups using longitudinal analysis with appropriate recognition for informative dropout.

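### The primary test ignores the randomisation strata, and the only stratified check named is continuity-corrected by centre: a small, avoidable loss of efficiency, not an invalid test

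*Protocol article*

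**What the plan says.** Under Randomization, patients are allocated 1:1 "with the following stratification factors: (1) research site, (2) pancreatic texture: soft versus normal/hard", and thirdly by pancreatic duct diameter, cut at 3 mm.

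Under Statistical methodology, the primary analysis is fixed without strata: "The two-sided, two-sample test for binomial proportions will be used to test for a difference in the probabilities of leak/fistula occurrence". The check on it is also fixed: "Sensitivity analysis will be performed using the continuity-corrected Cochran-Mantel-Haenszel (CMH) test calculated over the recruiting centers". The remaining model named for the primary outcome is descriptive of sites: "Logistic regression will be used to investigate the variation in these probabilities by center". The same section sets the two-stage boundaries for the standardised Z: at the interim, stop for no difference inside ±0.698 and for a difference beyond ±2.736; at the final analysis, reject beyond ±1.934.

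Under Sample size, 208 per group is planned to "detect a difference in proportions of 10 % (10 % versus 20 %) with power of 80 % and significance level of 0.05", using the same unstratified test.

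Both the Background and the Discussion criticise earlier studies for not stratifying by pancreatic consistency or duct diameter.

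**The concern.** The authors treat texture and duct diameter as factors that matter for fistula and balance the arms on them. The article's named analyses of the primary outcome then make no use of either.

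Balanced allocation within prognostic strata reduces the true variance of the difference in fistula rates. An unstratified standard error does not reflect that reduction, so the test rejects too rarely. What is at stake is some power, and an interim Z that is slightly too small when it is compared with the futility and efficacy limits.

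The sensitivity test has a separate weakness. A continuity correction shrinks the statistic whatever the centres look like. A check that is stricter than the primary test by construction cannot show whether centre differences explain a result.

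**Working it through.** **1. The plan's own figure.** Inputs from Sample size and Statistical methodology: 20 % v 10 %, 208 per group, interim at 208 of 416 patients (information fraction 0.5), limits 0.698 / 2.736 / 1.934. Expected final Z = 0.10 / √[(0.20×0.80 + 0.10×0.90)/208] = 0.10 / 0.03467 = 2.884. Bivariate normal integration over the limits gives two-sided error 0.0501 and power 80.1 %. The design reproduces, and for the unstratified test.

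**2. Why ignoring strata is conservative.** With stratum fistula rates p_k and overall rate p, p(1−p) = mean of p_k(1−p_k) + variance of p_k. The unstratified test uses the left side. Under stratified 1:1 allocation the true variance involves only the first term on the right. The gap is zero if the strata do not predict fistula, and grows as they do.

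**3. Size under the protocol's boundaries.** The document gives no prognostic strengths, so these are assumptions: odds ratios for soft texture / small duct as listed, each factor present in 50 % of patients, permuted blocks of 4, and 8 sites (site log-odds SD 0, 0.3, 0.5 and 0.5 by row). There were 6,000 simulated trials per cell; Monte Carlo error is about 0.3 points for type I error and 0.5 for power. Entries are type I error / power.

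| Odds ratios | Unstratified | CMH, all three factors, uncorrected | CMH by centre, corrected |
|---|---|---|---|
| none | 0.051 / 79.6 % | 0.050 / 79.5 % | 0.036 / 74.6 % |
| 2/1.5 | 0.044 / 81.8 % | 0.047 / 81.8 % | 0.032 / 76.3 % |
| 3/2 | 0.045 / 81.3 % | 0.054 / 82.7 % | 0.032 / 76.8 % |
| 5/3 | 0.036 / 81.7 % | 0.054 / 84.0 % | 0.027 / 76.9 % |

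A second simulation, with 10 sites and odds ratios from 2/1.5 to 4/3, gave these powers:
- unstratified: 80.7 to 81.6 %
- CMH over all 40 strata (10 × 2 × 2): 80.4 to 83.6 %
- CMH over texture x duct only: 81.2 to 83.7 %

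The differences from unstratified are −0.3 to 2.0 points for the 40 strata and 0.5 to 2.1 points for texture x duct. Unstratified error fell from about 0.05 to 0.04.

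**4. The continuity correction on its own.** In a single-look analysis at 1.96 with 8 sites and no stratum effect, the CMH by centre has error 0.049 and power 82.0 % uncorrected, against 0.037 and 78.0 % corrected. The cost is about 4 points, and none of it is due to centres.

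**5. A borderline table.** Take 42 v 27 fistulas of 208 each, as one table without centre strata (an illustration, not the planned test).
- Binomial test: p = 69/416 = 0.1659; Z = (15/208) / √[0.1659×0.8341×2/208] = 0.0721/0.0365 = 1.98, P = 0.048.
- Corrected CMH: expected count 34.5; V = 208×208×69×347 / (416²×415) = 14.42; Z = (7.5 − 0.5)/√14.42 = 1.84, P = 0.065.

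Against the final limit of 1.934 the first rejects and the second does not. Without the correction the CMH statistic is 7.5/3.798 = 1.97, which also rejects.

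**The case against.** The strongest defence is that nothing here is broken. The trial is sized for the unstratified test and analysed with it, error is not inflated, and the planned 80 % power is met. That stands.

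The gain from stratifying is also small and conditional. A further run under the two-stage boundaries (10 sites, 20,000 trials per cell) gave 80.7 % unstratified v 79.7 % for the 40-stratum CMH when texture and duct have no effect, and 81.7 v 82.7 % at odds ratios 4/3. Forty strata leave about 208/40 ≈ 5 patients each at the interim, and sparse strata carry little information. This too stands, and it is why site should not be crossed with the other factors unpooled.

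The sensitivity test decides nothing, since the stopping limits apply to the primary Z. Disagreement would also be uncommon: in about 4 % of simulated trials at 20 v 10 % (single look, 1.96) a significant primary result was not significant on the corrected test. That limits the weight of the point but does not justify the correction.

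Three stronger readings are tempting and unsupported:
- A reader might infer that the protocol contradicts itself by faulting earlier studies for not stratifying. It does stratify its randomisation on those factors.
- A reader might infer that texture and duct enter no planned analysis at all. The article names none for the primary outcome, but the analysis plan is not shown and may hold adjusted supportive models.
- A reader might infer that error is below 5 % and power lost whatever the data. Both depend on the strata predicting fistula.

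**Conclusion.** The mismatch between stratified randomisation and an unstratified primary test is real and stated outright in the article. Its cost is modest: about 0 to 2 points of power, and error about 0.05 down to 0.04, for assumed texture/duct odds ratios of 2/1.5 to 4/3 under the two-stage boundaries. These sizes rest on assumed odds ratios, prevalences, site numbers and block size. The direction needs only that the strata are prognostic.

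The continuity-corrected CMH by centre is conservative even when no stratum matters, so it is a poor check on the primary result. It would be wrong to call the primary test invalid or the trial underpowered: the test keeps its level and reaches its planned power. This is a worthwhile improvement in wording, not a defect that threatens the conclusion.

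**What to change.** - Make the primary test a CMH test without continuity correction, stratified by texture x duct diameter. Include site only after a pooling rule for small sites is written down in advance. An equivalent adjusted analysis reporting a marginal risk difference would also serve.
- Use that same Z at the interim and the final analysis against the stated boundaries, and settle this before the interim at 208 patients.
- Report the Mantel-Haenszel risk difference with its confidence interval.
- Keep the unstratified test as a sensitivity analysis.
- Drop the continuity correction from the CMH by centre.

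The cost is wording only: the factors are already recorded at randomisation, and sample size, visits and boundaries do not change. The downside is that sparse strata can cost up to about 1 point of power if the factors turn out not to be prognostic, which the restricted stratification is meant to limit.
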